**List other data variables**						
Symptoms and signs of RD			x	x	x	x
RD evolution time			x	x	x	x

The study is conducted at the Radiotherapy Oncology Center of the Reina Sofia Hospital and five participating Primary Care Centers. They are located in Cordoba (Spain) and depend on the Andalusian Health Service.

#### Eligibility criteria

Inclusion criteria are as follows: patients aged 18 years or older diagnosed with breast cancer and who are going to start radiation therapy with a radical intention on the affected breast, by the hypofractionated scheme with integrated boost (40.05 Gy with integrated boost, 48 Gy, in 15 sessions), coming from centers involved in the project or that can be followed up by a participating primary care professional and that sign an informed consent.Exclusion criteria are as follows: patients with dermal lesions or invasive skin cancer or distant metastases; history of connective tissue disorders; severe mental disorder (dementia, drug addiction, etc.); history of hypersensitivity reaction to any of the ingredients in the study cream; history of severe/extensive burn, moisture, erosion, or drainage in the treatment area; or participants involved in other clinical trials within that month.

Fourteen collaborating clinical researchers (5 oncologists, 8 GP, and one primary care occupational therapist) will perform the therapeutic intervention to be tested.

#### Who will take informed consent?

The radiation oncologists will collect the informed consent during the recruitment process. In the informed consent form, in case the recruited patients consent to participate, they will be asked if they accept the use of their data, even if they decide to drop out.

#### Interventions

Once the patient has been included in the study and allocated to one of the two groups, the radiation oncologists will collect demographics and existing pathologies and perform an initial assessment of the skin to be irradiated before the start of radiation therapy. The radiation oncologist will administer the patient a Quality-of-Life Assessment Questionnaire (Skindex-29) [19] and inform the family physician of the patient’s details, identification code, and probable date of initiation of radiation therapy so that the family physician can contact the patient prior to the start of the treatment to schedule follow-up visits.

At each follow-up visit after sessions 5, 10, and 15 and 1 week after completion of radiation therapy, the family physician will perform the following actions:

Evaluate patients’ irradiated skin according to the common toxicity criteria of the cooperative skin group suggested by the RTOG Foundation (https://www.rtog.org) [18].Likewise, patients presenting with dermatitis will be asked to assess and quantify the discomfort and pain related to dermatitis symptoms and signs on an analog ordinal scale (from 1 to 10).Complete the Skindex-29 Quality of Life Questionnaire [19] (https://www.bibliopro.org/buscador/294/cuestionario-dermatologico-de-calidad-de-vida-skindex-29).Record adverse events (AE): Possible AE will be evaluated and reported during the study, and their causal relationship with the components of the cream will be assessed. If an adverse reaction is found, the researcher will evaluate the intensity and frequency of each episode and decide whether or not additional treatments are needed. These side effects will be notified to the Andalusian Pharmacovigilance Center through the yellow card alert system. If the physician considers it appropriate, the patient will be withdrawn from the study.

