**List outcome variables**						
Presence/absence of radiodermatitis (RD)			x	x	x	x
Toxicity Level (ORTG Criteria)			x	x	x	x
Degree of discomfort with RD			x	x	x	x
Quality of life related to health			x			x
Presence of adverse events			x	x	x	x

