**Secondary outcomes**	
Onset and duration of RD	Time of onset and duration of post-radiation dermatitis
Toxicity in patients’ irradiated skin	Common toxicity criteria of the cooperative group for skin suggested by the RTOG Foundation (https://www.rtog.org) [18]
Discomfort and pain concerning symptoms and signs related to dermatitis	Degree of skin discomfort caused by radiation. Subjective assessment and quantification by the patient on an ordinal scale (0 to 10) Pruritus, pain, itching, or peeling of the skin
Quality of life	Quality of life of patients with skin conditions Skindex-29 questionnaire [19]

In addition, secondary outcomes include the level of toxicity in patients’ irradiated skin. It will be assessed according to the common toxicity criteria of the cooperative group for skin suggested by the RTOG Foundation (https://www.rtog.org) [18] according to which toxicity is classified into five levels: 0 for no toxicity or no change; 1 for scattered macular or papular rash or erythema that is asymptomatic; 2 for scattered macular or papular rash or erythema with pruritus or other associated symptoms; 3 for symptomatic generalized macular, papular, or vesicular rash; and 4 for exfoliative dermatitis or ulcerative dermatitis.

The assessment of discomfort and pain concerning symptoms and signs related to dermatitis is based on the subjective assessment and quantification by the patient on an ordinal scale (range 0 to 10), the Visual Analogic Scale (VAS), answering the following question: What score would you rate from 0 (where 0 is the situation where you do not feel symptoms such as pruritus, pain, itching, or peeling of the skin) to 10 (where 10 is the situation where you notice the most symptoms) to your skin problem where do you have the lesion?

Quality of life will be assessed by completing the Skindex-29 questionnaire. Skindex-29 is a self-administered questionnaire to measure the quality of life of patients with skin conditions every 4 weeks, consisting of 29 items. The Spanish version of Skindex-29 has been validated [19].

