## Statistical methods

After the mechanization and filtering of the data, a descriptive analysis will be performed that will include the characteristics of the studied population (sociodemographic variables) and outcome variables using measures of central tendency, dispersion, and position in the quantitative variables and tabulation and calculation of relative frequencies in qualitative variables. The calculation of the main estimators with their corresponding confidence intervals for 95% safety will also be performed. An intention-to-treat analysis will be performed. To minimize the problem of missing data, the analysis will be performed by dragging the data from the visit from which they are obtained to the following visits and to the final one. That is, the intent-to-treat analysis will include all participants assessed at least once after randomization. In addition, a per-protocol analysis will be performed, defined as the group of participants who comply with the procedure to be followed, including the use of the substances tested in the study, in at least 80%. A pre-post-intervention comparative analysis will then be performed with the endpoints used; for this, we will use means comparison tests taking into account the results obtained in each of the visits (parametric, such as ANOVA for repeated measures, if the variables follow a normal distribution—Shapiro-Wilk Test—or non-parametric, such as Friedman’s test, if they do not follow it), or proportion comparison test on qualitative variables, such as Pearson’s chi-square test or Fisher’s exact test (*p* < 0.05). Finally, the results will be statistically compared between groups using the log-rank test after estimating the survival curve with the Kaplan-Meier method. Multiple linear regression analysis-dependent variable: results obtained with the VAS, and the survival analysis, by Cox regression-dependent variables: RD or no; RD improvement vs. no improvement and cured vs. non-cured will be performed to evaluate the effect of the product, adjusting for the sociodemographic and clinical variables presumably predictive or confounding. Statistical analysis will be performed using SPSS v.17.0 and EPIDAT 4.1 packages.

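### As the Interventions section reads, discomfort (VAS) is asked of patients with dermatitis, so the VAS regression conditions on the primary outcome; the 1 to 10 and 0 to 10 scales also conflict

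*Protocol article*

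**What the plan says.** **Who is asked.** In the list of actions at each follow-up visit (Interventions), "patients presenting with dermatitis will be asked to assess and quantify the discomfort and pain related to dermatitis symptoms and signs", and the scale is described as "on an analog ordinal scale (from 1 to 10". Skin toxicity and Skindex-29, in the same list, carry no such condition.

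**How the outcome is defined.** Table 2 has "Subjective assessment and quantification by the patient on an ordinal scale (0 to 10". The text below it sets the lower anchor: "0 is the situation where you do not feel symptoms such as pruritus, pain, itching, or peeling of the skin". No restriction to RD is stated there, but the question put to the patient ends "to your skin problem where do you have the lesion". Table 1 lists the item as "Degree of discomfort with RD" at all four follow-up time points.

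**How it is analysed.** Statistical methods specifies "Multiple linear regression analysis-dependent variable: results obtained with the VAS", to evaluate the effect of the product with adjustment for sociodemographic and clinical variables. The same section states that "the intent-to-treat analysis will include all participants assessed at least once after randomization", with earlier values carried forward to later visits. It does not say how a patient without RD enters the VAS regression.

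**What it serves.** Secondary objective (a) asks whether the preparation reduces discomfort. RD incidence is the primary outcome, and the Sample size section expects 46.7% in the experimental group (EG) and 78.6% in the control group (CG).

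**The concern.** Randomisation makes the arms comparable as randomised. It does not make comparable the subsets that later develop RD, because the cream is meant to change who develops it. If a VAS score exists only when RD is present, availability of this outcome is decided after randomisation by the primary outcome. EG reporters are then those whose dermatitis the cream failed to prevent, while CG reporters also include patients whose dermatitis the cream would have prevented.

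Neither device in the plan repairs this. Adjusting for sociodemographic and clinical covariates does not restore comparability lost by conditioning on an outcome. Carry-forward has nothing to carry for a patient who never has RD. The collection rule in Interventions therefore cannot supply the intention-to-treat population that Statistical methods announces. At stake is secondary objective (a): a real benefit could be diluted or, under some conditions, appear as harm.

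The scale conflict adds to this. On the 1 to 10 version a symptom-free patient has no valid score. On the 0 to 10 version the score is 0.

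**Working it through.** **Inputs from the protocol (Sample size):** RD 46.7% in EG and 78.6% in CG, alpha 0.05, power 80%, 1:1 allocation, 20% loss, 88 patients. The protocol gives no VAS mean, SD or severity distribution, so every VAS value below is an assumption.

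**1. The plan's own figure.** Two-sided comparison of two proportions without continuity correction:

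n = [1.96·√(2·0.6265·0.3735) + 0.8416·√(0.467·0.533 + 0.786·0.214)]² / 0.319² = 34.9, so 35 per arm.

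35/0.8 = 43.75, so 44 per arm and 88 in total. This reproduces the stated figure.

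**2. Who would supply a VAS score.** At 35 evaluable per arm: 0.467 × 35 = 16.3 in EG and 0.786 × 35 = 27.5 in CG. At the full 44 per arm: 20.5 and 34.6.

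**3. When the sign reverses.** Suppose the cream only prevents RD and never causes it. Patients then fall into three groups: RD under either cream (46.7%), RD prevented by the cream (78.6 − 46.7 = 31.9%), and no RD under either (21.4%). Let A be the mean control VAS in the first group, P the mean control VAS in the second, and b the true relief the cream gives in the first.

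- RD-only, EG: A − b
- RD-only, CG: (0.467A + 0.319P)/0.786 = A − 0.406(A − P)
- RD-only difference, EG − CG: 0.406(A − P) − b

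The RD-only difference favours control whenever b < 0.406(A − P). The share 0.406 = 0.319/0.786 is also the fraction of CG reporters with no reporting counterpart in EG.

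With RD-free patients scored 0, the difference is −0.467b − 0.319P, which keeps the right sign.

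| A | P | b | RD-only EG − CG | All patients EG − CG |
|---|---|---|---|---|
| 5 | 2 | 0.5 | +0.72 | −0.87 |
| 5 | 2 | 1.0 | +0.22 | −1.10 |
| 5 | 2 | 1.5 | −0.28 | −1.34 |
| 5 | 3 | 0.5 | +0.31 | −1.19 |
| 5 | 4 | 0.5 | −0.09 | −1.51 |
| 5 | 5 | 0.5 | −0.50 | −1.83 |

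For the first row, simulated with 35 per arm and SD 1.5, the RD-only estimate favours control in about 90% of trials and does so significantly in about 20%.

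**4. Uniform shift.** Let latent severity be normal, with RD present above zero, VAS proportional to the excess, and the cream lowering everyone equally so that the RD rates match the protocol. Mean severity among RD patients is 0.77 (EG) versus 1.16 (CG), a gap of 0.40 in the right direction. Over all patients the gap is 0.56. At 35 per arm (Welch t-test), power is about 47% in RD patients only and about 90% in all patients.

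**5. An extreme case.** Let severity be uniform on 1 to 10 in CG RD patients. The cream prevents exactly the mildest 40.6% of cases and gives no relief to the rest. The EG mean is (1 + 9 × 0.406 + 10)/2 = 7.33 against 5.5 in CG. Over all patients it is 0.467 × 7.33 = 3.42 against 0.786 × 5.5 = 4.32. The RD-only test is significantly wrong in about 80% of simulated trials. That falls to about 54% with 0.5 points of relief in remaining cases, 25% with 1 point and 1.6% with 2 points. With no relief, the all-patient t-test detects the benefit in only about 18 to 19% of trials.

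**The case against.** **That only RD patients are asked is a reading.** The protocol never says so outright. The outcome definition has a zero anchor and no restriction, Table 1 schedules the item at every visit, and the intention-to-treat definition covers everyone assessed. If every patient is in fact scored, the bias disappears. This stands as a limit on certainty. Against it, the Interventions text names the patients to be asked, its range has no zero, the Table 1 label refers to RD, and the question presupposes a lesion. If the wider reading is right, the two sections still conflict on range and apparently on who answers, and sites could collect different data.

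**A reader might infer that the trial will probably show the cream as harmful.** The documents do not support that. The 80% figure needs prevention of exactly the mildest cases and no relief in any other. Modest relief shrinks it quickly, and a uniform shift keeps the right sign.

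**A reader might infer that objective (a) cannot be answered at all.** That is also too strong. Discomfort among patients with lesions is a relevant description, and toxicity grade (grade 2 requires symptoms) and Skindex-29 are collected without the restriction.

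**Scoring RD-free visits as 0 is itself an assumption.** This stands. Toxicity grade 1 is asymptomatic, so RD and symptoms are not the same thing, and the zeros make the VAS contrast partly repeat RD incidence.

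**A statistical analysis plan may settle who enters the regression.** It may, but it cannot recover answers that the collection rule did not request.

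**Conclusion.** The point holds as a should-fix. Followed as Interventions reads, the VAS regression compares about 16 with about 28 patients selected by the primary outcome, and it cannot be read as a randomised treatment effect. The size and direction of the distortion are unknown, because the protocol gives no VAS distribution. It ranges from loss of power (about 47% against 90% under a uniform shift) to a wrong sign when relief in remaining cases is less than about 0.41 times the severity gap between remaining and prevented cases. These results rest on the protocol's RD rates, 35 evaluable per arm, a score of 0 for RD-free patients and, for the sign condition, a cream that never causes RD.

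The scale conflict is certain. The restriction to RD patients is the more natural reading but not an explicit statement. One secondary outcome and objective (a) are affected. The RD incidence analysis and N = 88 are not.

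**What to change.** **In the text.** Reconcile Interventions with Outcomes on the single 0 to 10 scale. Direct the question to every patient at every follow-up visit, worded so that a patient without a lesion can answer. State that the VAS regression includes all assessed randomised patients, using a rank or ordinal model or robust standard errors because there will be many zeros. Prospectively this costs one question at visits already scheduled, one line on the case report form and one sentence of analysis wording.

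**For the data in hand.** Trial status says the study concluded in June 2023, so the prospective change may no longer be available. First establish whether RD-free patients were asked, and on which range. Where they were not, score attended RD-free visits as 0 by the Outcomes anchor. RD presence is scheduled at all four visits, so this needs no new data. State that this is an imputation that assumes no RD means no symptoms and partly repeats RD incidence. Report the RD-only comparison as descriptive.

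**Limit.** The all-patient analysis restores the direction of the comparison but does not guarantee power, as the 18 to 19% in the extreme case shows.

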#### Withdrawals or dropouts from the trial

Those patients meeting the selection criteria and willing to participate in the study who could not do so because they do not have the means to travel to the primary care center that corresponds to them will be offered the possibility of being followed up in the radiation oncology service. In addition, possible deviations from the protocol, discontinuities in visits, withdrawals, losses, and their reasons will be collected in a registry of incidents occurring during the follow-up of patients. In case the patient expresses her request to drop out of the trial for any reason, she will be withdrawn from the trial. Likewise, those patients who, by clinical criteria, the field investigator considers their discontinuation will be withdrawn. Patients lost to follow-up due to not attending the visits, death, and other reasons evaluated by the research team will also be recorded.

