#### Outcomes

All outcomes are described in detail in Table 2. The primary outcome is the incidence of RD.

**Table 2 Tab2:** Primary and secondary outcomes

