### Adverse event reporting and harms

Possible AE will be evaluated and reported during the study, and their causal relationship with the components of the cream will be assessed. If an AE is found, the researcher will evaluate the intensity and frequency of each episode and decide whether additional treatments are needed. These AE will be notified to the Andalusian Pharmacovigilance Center and the Ethics Committee of the Reina Sofia Hospital (Cordoba, Spain). If the physician considers it appropriate, the patient will be withdrawn from the study.

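### Patients can be withdrawn from the study on clinical judgement with no provision for further outcome assessment, and carry-forward then fills visits that could still have been held

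*Protocol article*

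**What the plan says.** Three places in the Protocol article govern discontinuation.

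- *Withdrawals or dropouts from the trial* first covers patients who ask to leave. It then adds, as a parallel case, that "those patients who, by clinical criteria, the field investigator considers their discontinuation will be withdrawn". The clinical criteria are not specified.
- *Adverse event reporting and harms* ends with "If the physician considers it appropriate, the patient will be withdrawn from the study". The list of follow-up visit actions under *Interventions* carries the same rule, directly after the handling of adverse reactions.
- What is kept about such patients is administrative: "withdrawals, losses, and their reasons will be collected in a registry of incidents occurring during the follow-up of patients". On consent, "they will be asked if they accept the use of their data, even if they decide to drop out". That concerns use of data, not further assessment.

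*Statistical methods* sets the missing-data rule, "dragging the data from the visit from which they are obtained to the following visits and to the final one", and the analysis set: "the intent-to-treat analysis will include all participants assessed at least once after randomization".

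*Outcomes* says "The primary outcome is the incidence of RD". Table 2 lists evaluation of the skin lesion beside it as a primary outcome. Skin is assessed after sessions 5, 10 and 15 and one week after radiotherapy ends.

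**The concern.** An intention-to-treat comparison needs the outcome of every randomised patient, whether or not the product was continued. Here a clinical decision can end participation, and nothing stated keeps the remaining visits going. The missing data are then partly created by the protocol. In the adverse-event text the decision follows a reaction to a topical product, so it may be related to the condition of the skin.

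The consequence depends on when the patient is withdrawn:

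1. **Before any post-randomisation assessment.** The patient leaves the intention-to-treat set as defined.
2. **After at least one assessment, with no RD recorded.** Carry-forward fixes the patient as RD-free, although the remaining visits could have shown RD.
3. **With RD already recorded.** Incidence is kept. The later course is lost: lesion evaluation (also listed as primary), duration, toxicity level and discomfort score.

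A statistical analysis plan can choose a better imputation method, but it cannot supply observations that were not made.

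**Working it through.** **Inputs from the Protocol article (Sample size).** Expected RD 46.7% with Alantel and 78.6% with control; alpha 0.05; power 80%; 1:1 allocation; 20% loss; 44 per group.

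**The plan's own figure.** With pooled variance under the null, two-sided, no continuity correction:

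n = [1.960·√(2·p̄·(1−p̄)) + 0.842·√(p₁(1−p₁) + p₂(1−p₂))]² / (p₂−p₁)², where p̄ = (0.467 + 0.786)/2 = 0.6265

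= [1.960·√0.4680 + 0.842·√0.4171]² / 0.319² = 34.9, so 35 per arm.

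35/(1 − 0.20) = 43.75, so 44 per arm and 88 in all. This matches the plan, so the sample size is not at issue.

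**Assumptions not in the documents.** Withdrawal shares by arm; RD status at withdrawal; how many of those withdrawn would later have developed RD; and a pooled z test (two-sided 0.05) on the carried-forward proportions. Results are exact: binomial probabilities with 44 per arm are summed over all pairs of counts for which the test is significant in favour of Alantel.

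**Illustration A: no true effect.** True RD is 78.6% in both arms. Let d be the share of the Alantel arm withdrawn RD-free who would all later have had RD. The observed Alantel rate is 0.786 − d.

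| d in Alantel | Control: none | Control: d/2 | Control: d |
|---|---|---|---|
| 0 | 2.7% | 2.7% | 2.7% |
| 5% | 8.3% | about 5% | about 2.7% |
| 10% | 19.1% | about 8% | about 2.7% |
| 15% | 35.1% | about 12% | about 2.7% |

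Entries are probabilities of a significant result favouring Alantel. In patients, 10% is 0.10 × 44 = 4.4 and 15% is 6.6. If RD-free withdrawals would develop RD only at the arm's own rate, d = 15% needs 0.15/0.786 = 19% of the arm to be withdrawn RD-free.

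**Illustration B: planned effect.** Let w be the share withdrawn RD-free, with later RD at the arm's own rate. The observed rate is p(1 − w).

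- w = 0: 46.7% v 78.6%, difference 31.9 points, exact power about 89%.
- w = 10% in both arms: 0.467 × 0.9 = 42.0% v 0.786 × 0.9 = 70.7%, difference 28.7 points, power about 78%.
- w = 20% in both arms: 0.467 × 0.8 = 37.4% v 0.786 × 0.8 = 62.9%, difference 25.5 points, power about 66%.
- w = 20% in Alantel only: 78.6 − 37.4 = 41.2 points.
- w = 20% in control only: 62.9 − 46.7 = 16.2 points.

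So the error can go either way, and equal withdrawal still costs effect size and power.

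**The case against.** A reader might infer more than the text supports, in three ways.

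**That stopping the cream always means leaving the study.** The withdrawals section does not mention the cream. The per-protocol set in Statistical methods requires at least 80% compliance, including product use, and stands beside an intention-to-treat set. That implies under-users can stay in the study. This objection stands: the rule reaches patients whom a physician or investigator withdraws, not everyone who stops or skips the product.

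**That observation stops just as RD appears, so a more irritating cream looks better.** The visit actions list skin grading first and the adverse-event step last, and grade 1 toxicity already includes asymptomatic erythema. A reaction in the irradiated field seen at a visit would normally be graded before withdrawal, and carry-forward would then repeat RD as present. RD has no stated grade cut-off, so this too is an inference, but it is enough to leave the direction of bias open. For incidence, the problem is confined to patients withdrawn with no RD recorded.

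**That the planned 20% loss measures the exposure.** It is an all-cause allowance for sample size. No document gives a rate of physician-decided withdrawal, and the largest false-win figures need nearly that whole allowance from one cause in one arm.

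Two further points have some force. Statistical methods also names Kaplan-Meier curves with a log-rank test and does not say how withdrawn patients enter them, so the z test used here is one choice among several. And an article may leave detail on follow-up after withdrawal to the full protocol. Against that, withdrawal from the study is stated outright and more than once, with no qualification that follow-up continues.

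**Conclusion.** The concern holds in a limited form. As written, physician- or investigator-decided withdrawal takes a randomised patient out of the study, no later assessment is provided for, and carry-forward substitutes for it. Incidence is at risk in patients withdrawn with no RD recorded, and the later course of RD in the others. Patients never assessed leave the intention-to-treat set.

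Neither the size nor the direction of the bias can be fixed from the documents. The rise in false wins from 2.7% to as much as 35.1% is an extreme case that rests on one-sided withdrawal and later RD in every affected patient. It largely shrinks when control has half the share and disappears when the shares are equal. The loss of power from about 89% to 66% needs no imbalance, but it does assume that 20% of each arm is withdrawn RD-free. The documents do not support a claim that the plan favours Alantel. This is a gap worth closing because closing it is cheap; it does not show that the result would be wrong.

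**What to change.** In *Interventions*, *Withdrawals or dropouts from the trial* and *Adverse event reporting and harms*, separate stopping the study product from leaving follow-up:

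- A patient discontinued by the physician or investigator stays in the remaining planned visits. RD, toxicity level, the discomfort score and Skindex-29 are recorded there as scheduled, together with the date the product was stopped.
- The patient is analysed in the randomised group.
- Only withdrawal of consent to follow-up ends data collection.

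When and why the product is stopped remains the clinician's decision, unchanged.

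The cost is a change of wording plus, for a few patients, attendance at visits that are already scheduled (at most three after the first).

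*Trial status* says the study concluded in June 2023, so these visits can no longer be added to this trial. What remains possible is to report, by arm, how many patients were withdrawn by clinical decision, at which visit and with what RD status. The primary comparison can then be shown under contrasting assumptions for those withdrawn RD-free.
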